### Operative details

All surgeries will be done under general anesthesia with tracheal intubation. Anesthesiologists monitor and record the following parameters during surgery: electrocardiogram (ECG), heart rate (HR), blood pressure (BP), respiratory rate (RR), oxygen saturation (SpO_2_), end-tidal CO_2_ (EtCO_2_), temperature, urine volume, and blood gases. Protective lung ventilation with a tidal volume of 6 to 8 ml/kg of predicted body weight, a PEEP of 6 to 8 cmH_2_O will be used. Postoperatively, patients will be transferred to the ward or ICU depending on their condition. Intravenously administered, patient-controlled analgesia with sufentanil will be used for postoperative analgesia.

At the end of the surgery, the information is recorded according to the Checklist. Symptoms are recorded. All chest radiographs and computed tomograms (CTs) are evaluated for infiltrates and atelectasis by the attending radiologist, who is unaware of the intervention applied.

The investigators enter all data into a central database for the trial. A summary of each patient data record is forwarded to the principle investigator of each center 30 days after surgery for inspection. When follow-up finishes, the patient records are transmitted to the statistical coordinating center for editing and analysis.

Patients are excluded from the protocol analysis if they did not meet the inclusion criteria, fulfilled an exclusion criterion, had no in-hospital evaluation of the outcomes or had no follow-up visit.

### Outcome measurement

*The primary outcome* is postoperative pulmonary complications occurring within 30 days after surgery.

Postoperative pulmonary events are scored on an ordinal scale of 1 to 4 (see supplementary material 3). A clinically significant postoperative pulmonary complication is defined as two or more items in the grade-2 complications or one item in the grade-3 or grade-4 complications.

*Secondary outcomes* include the incidence of postoperative pulmonary complications within 30 days after surgery; all-cause mortality within 30 days and 1 year after surgery; admission to the intensive care unit (ICU) and length of ICU stay within 30 days after surgery; the length of postoperative hospital stay; and medical costs during hospitalization after surgery.

### Sample size calculation and statistical analysis

To calculate sample size, we used available data from the pilot study in our hospital on postoperative pulmonary complication incidence (unpublished). In the study, the incidence of postoperative pulmonary complications was 23% in the ST-36 TEAS group and 32% in the Control. Assuming an additional decrease by 9% in group DT (14%), with a power of 80% at the *P* = 0.05 level of statistical significance, 345 patients (*N* = 115 for each group) are needed.

Statistical analysis will be performed by the Department of Statistics of the Fourth Military Medical University. The statistician is blinded from the allocation of groups. SPSS19.0 statistical software packages will be used to analyze the data. Prior to all analyses, a detailed statistical analysis protocol was developed. The intention-to-treat (ITT) population was defined as the patients who are randomized and received at least one treatment session. The per-protocol (PP) population was defined as the patients who completed the study and did not have major protocol violations. All analyses were based on the ITT population and the PP population. The result of the ITT analysis will be compared with that of the PP analysis to check whether the results are consistent.

All data will be checked by two investigators. We compare postoperative variables with either Student’s *t* test or the Mann-Whitney *U* test for continuous variables, depending on the characteristics of the variables, and we use the *χ*^2^ test for categorical variables. We compare both the composite primary outcome of incidence of postoperative pulmonary complications within 30 days after surgery and the secondary outcome of occurrence of systemic inflammatory response syndrome (SIRS) complications by postoperative day 30 with an unadjusted *χ*^2^ test, weighting every individual complication equally. Comparison between the groups is made by analyzing data with the post-hoc method. Where appropriate, we express statistical uncertainty with 95% confidence intervals (CIs). We calculate Kaplan-Meier estimates of survival curves, and we use log-rank tests to compare survival distributions between study groups. We will censor data used for Kaplan-Meier estimates when patients do not have a postoperative pulmonary complication during the study period. Analyses are performed using SPSS 13.0 software and a two-sided *P* < 0.05 was considered statistically significant.

Interim analyses are performed after half the required participants had been enrolled (*n* = 173). If the Institutional Review Board thought it was no longer ethical to withhold TEAS from the patients in the non-acupoint and Control groups based on the results of the interim analysis with pulmonary complications as the endpoint, the study will be stopped.

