**Discussion:**

The result of this trial (which will be available in September 2019) will confirm whether TEAS before and during anesthesia could alleviate the postoperative pulmonary complications after gastrointestinal surgery in elderly patients, and whether dual-acupoint stimulation is more effective than single-acupoint stimulation.

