## Background

Life expectancy has been increasing in recent years. In parallel with the increase of life expectancy, the number of elderly patients undergoing surgery is rising. Some of the diseases, such as gastrointestinal cancers, are predominant diseases of this elderly population and the major causes of morbidity and mortality. It had been reported that more than 30% patients with gastric cancer were older than 70 years [1]. Age exceeding 70 years is an independent predictor of increased postoperative complications, in-hospital mortality, and longer hospital stays [2]. Among the postoperative complications, pulmonary complications are closely related to general anesthesia. Atelectasis develops within minutes after the induction of general anesthesia [3] and age is a risk factor of pulmonary complications. Almost all mechanically ventilated, elderly patients developed atelectasis and shunting during anesthesia [4].

Acupuncture is an integral part of an ancient Chinese system of medicine that has been used for more than 2500 years to treat diseases and relieve pain. The use of acupuncture during anesthesia, which is called anesthesia-assisted-anesthesia, is promising in three aspects [5–7]: decreasing the need for anesthetics such as opioids, alleviating adverse events, and exerting organ-protective effects. Electrical stimulation of acupoints, which includes electroacupuncture and transcutaneous electric acupoint stimulation (TEAS), was developed as an alternative to manual acupuncture. Electrical stimulation has several advantages over manual stimulation, such as causing less pain, being less time consuming, and with better standardization.

However, whether the more acupoints stimulated the better the benefit is still in debate. Though according to the Traditional Chinese Medicine (TCM) theory, combinative stimulation of acupoints is important, some investigators found that there was no difference between dual-acupoint and single-acupoint stimulation [8]. In this study, we hypothesize that TEAS before and during surgery would decrease the morbidity or mortality of major postoperative pulmonary complications at 30 days after gastrointestinal surgery in elderly patients, and dual-acupoint stimulation would be better than single-acupoint stimulation.

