## Discussion

The result of this trial is expected to provide convincing evidence that TEAS is effective for improving postoperative outcomes in older patients undergoing gastrointestinal surgery, and that dual-acupoint TEAS is better than single-acupoint.

TEAS is an alternative technique to acupuncture. Compared with acupuncture, it is easier and safer for non-acupuncturists to use. The use of acupuncture-related techniques during anesthesia may benefit patients considerably, especially by decreasing anesthetic consumption and reducing adverse events [6–11]. We have used electroacupuncture in clinical settings and obtained positive results. In healthy volunteers, we proved that electroacupuncture could alleviate low-perfusion-induced cerebral dysfunction [12]. In both adult and pediatric patients undergoing cardiac surgery, we proved that TEAS could improve cardiac outcomes and shorten ICU stays [13, 14]. Based on these evidences, we speculated that TEAS pretreatment would activate the endogenous protective mechanism, and then protect patients against subsequent surgical stress. We believe that this intervention will reduce the subsequent incidence, duration, and severity of organ dysfunction, and further reduce the morbidity and mortality. However, whether the more acupoints stimulated the better the benefit is still not clear. According to the TCM theory, combinative stimulation of acupoints is important. But Alizadeh et al. found that there was no difference between dual-acupoint and single-acupoint stimulation for treating postoperative nausea and vomiting [8].

However, currently there is not enough evidence for acupuncture based on strict clinical trial of evidence-based medicine because of the poor quality of current studies, such as small sample size, no description of methods for randomization, no standardized acupuncture protocol which may lead to performance bias, and so on. In this trial, we used a central randomization, multicenter design, standardized acupuncture protocol, with a large sample size to ensure power. A major issue in planning the design of this trial is which control should be used. Since the primary consideration of this trial is to clarify whether TEAS is effective in reducing postoperative complications, we all agree that both a non-acupoint Control group and a no-stimulation Control group are needed.

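### The single 80% power figure for 345 patients holds for the overall three-arm test and for dual versus Control, but dual versus single has only about 42% power and single versus Control about 33%

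*Protocol article*

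**What the plan says.** In the protocol article, Sample size calculation and statistical analysis, the pilot data are summarised as "the incidence of postoperative pulmonary complications was 23% in the ST-36 TEAS group and 32% in the Control". The dual-acupoint rate is an assumption, a further 9 points lower: "Assuming an additional decrease by 9% in group DT (14%), with a power of 80" per cent. The conclusion is that "345 patients (*N* = 115 for each group) are needed". No comparison is attached to the power figure. The same section says "a two-sided *P* < 0.05 was considered statistically significant", plans an unadjusted chi-square test for the primary outcome, and leaves comparisons between groups to a post-hoc method that it does not name.

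The aims are partly pairwise. The Background includes in the hypothesis that "dual-acupoint stimulation would be better than single-acupoint stimulation". The Discussion part of the Abstract says the result will confirm, among other things, "whether dual-acupoint stimulation is more effective than single-acupoint stimulation". The main Discussion expects convincing evidence that dual is better than single, and describes the trial as one "with a large sample size to ensure power".

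**The concern.** Three planning rates give three pairwise contrasts of very different size: 18 points for dual versus Control, and 9 points each for dual versus single and single versus Control. One sample size cannot give all of them the same power. The power figure follows directly on the assumed extra 9-point fall in the dual arm, so a reader may well take 80% to cover dual versus single.

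If it does not, one of the headline questions is likely to end in a non-significant result even when the planning rates are exactly right. In a trial presented as large enough to ensure power, that result could be taken to mean that a second acupoint adds nothing. The article already cites a study that found no difference between dual and single stimulation, so such a reading would have something to attach to.

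**Working it through.** **Inputs**, all from Sample size calculation and statistical analysis: Control 0.32, single 0.23, dual 0.14; n = 115 per arm; two-sided alpha 0.05; target power 80%. The calculations assume every patient contributes an outcome and there is one final analysis.

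**Pairwise formulas** (pooled variance under the null). With d = p1 − p2 and p̄ = (p1 + p2)/2:

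- s0 = √[2p̄(1 − p̄)]
- s1 = √[p1(1 − p1) + p2(1 − p2)]
- power = Φ[(d√n − z·s0)/s1]
- n per arm for 80% = [(z·s0 + 0.8416·s1)/d]²

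Here z = 1.960 at alpha 0.05 and z = 2.394 at 0.05/3.

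**Can the plan's 115 be reproduced?** At two-sided 0.05, 80% power needs:

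- dual versus Control: 85 per arm (96 with continuity correction)
- overall three-arm test: 106
- dual versus single: 292 (313 with continuity correction)
- single versus Control: 386 (408 with continuity correction)

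None of these is 115. Dual versus Control comes to 114 per arm with alpha 0.05/3, or with alpha 0.025 plus continuity correction. Either would explain the figure, but the article states neither adjustment. No variant tried for the two 9-point contrasts, one-sided or two-sided, comes near 115; the smallest is 230.

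**Overall test, 2 degrees of freedom.** The mean rate is (0.32 + 0.23 + 0.14)/3 = 0.23. The noncentrality is 115 × (0.09² + 0² + 0.09²)/(0.23 × 0.77) = 10.52. Against the critical value 5.991, power is 83.6%. Power first reaches 80% at 106 per arm.

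**Pairwise power at 115 per arm:**

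| Contrast | d | s0 | s1 | (d√115 − 1.960·s0)/s1 | Power, alpha 0.05 | Power, alpha 0.05/3 | n per arm for 80%, alpha 0.05 (0.05/3) |
|---|---|---|---|---|---|---|---|
| Dual v Control | 0.18 | 0.5951 | 0.5814 | 1.314 | 90.6% | 80.8% | 85 (114) |
| Dual v single | 0.09 | 0.5491 | 0.5454 | −0.204 | 41.9% | 26.1% | 292 (389) |
| Single v Control | 0.09 | 0.6315 | 0.6283 | −0.434 | 33.2% | 19.2% | 386 (515) |

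At alpha 0.05, 80% power for dual versus single would mean 3 × 292 = 876 patients in three arms, and for single versus Control 3 × 386 = 1,158.

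**Simulation check** (200,000 trials at the planning rates, alpha 0.05): overall 84.7%, dual versus Control 91.1%, dual versus single 42.2%, single versus Control 33.7%. Dual is significantly better than both other arms in about 41% of trials. All three pairs are significant in about 7%.

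**Expected precision for dual minus single.** The 95% half-width is 1.96 × √[(0.14 × 0.86 + 0.23 × 0.77)/115] = 1.96 × √(0.2975/115) = 0.0997. That is about 10 points around an assumed difference of 9, so an interval centred on the planning difference would include zero.

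**The case against.** The strongest reply is that the article contains no arithmetic error. It lists three rates, then a chi-square test, then post-hoc comparisons. Sizing on the overall three-group test is a natural reading, and 115 per arm exceeds the 106 needed. A condensed article may also leave naming the powered comparison to the full document. This stands as far as it goes: the 345 is not shown to be wrong, and it delivers at least 80% for two comparisons. But a significant overall test does not say whether dual differs from single, and no analysis plan can raise the power that 115 per arm gives that contrast. A plan can only disclose it.

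A reader might infer from the low pairwise figures that the trial cannot show whether TEAS works. The documents do not support that. The Discussion names the effectiveness of TEAS as the primary consideration, and dual versus Control addresses it with 91% power, or 81% after a three-way Bonferroni adjustment. Low power is also not zero power: at the planning rates, dual versus single still succeeds in about four trials in ten at unadjusted 0.05.

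It is also fair to say that unadjusted figures presuppose a choice the article has not made, since the post-hoc method is unnamed. That is why both sets are shown. Finally, misreading of a null result is a prediction, and the plan does allow for 95% confidence intervals where appropriate. The Abstract's wording is neutral about direction. It nevertheless promises confirmation, and the main Discussion goes further by expecting evidence that dual is better.

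**Conclusion.** The point holds as a mismatch between power and stated aims. The single 80% figure is met for the overall three-arm test (84%) and for dual versus Control (91% unadjusted, 81% with Bonferroni over three pairs). It is not met for dual versus single (42%, or 26%) or single versus Control (33%, or 19%). If the planning rates are exactly true, the trial misses the dual-versus-single difference about 58% of the time at unadjusted 0.05 (100 − 41.9).

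These figures rest on the article's own rates, full follow-up and no allowance for the planned interim look. Losses would lower all of them. The conclusion for the two 9-point contrasts does not depend on the choice of formula or on whether the test is one-sided: one-sided power at 0.05 is still only 55% and 45%. It should not be stretched to a claim that 345 was miscalculated, or that the trial cannot test TEAS against no stimulation.

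**What to change.** No change to enrolment or allocation is proposed.

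1. In the sample-size paragraph, state that 345 patients give at least 80% power, at the planning rates, for the overall three-arm chi-square test already planned and for dual versus Control.
2. List the power of each pairwise contrast beside its alpha, matched to the post-hoc adjustment that will be used: 91% / 42% / 33% (dual v Control, dual v single, single v Control) at unadjusted two-sided 0.05, or 81% / 26% / 19% with Bonferroni over three pairs. Another method needs its own figures.
3. Report dual versus single and single versus Control as risk differences with 95% confidence intervals. Give the expected half-width of about 10 points for dual minus single, and state that a non-significant result there is not evidence of equal effect.
4. Reword the Discussion part of the Abstract and the main Discussion so that they do not promise confirmation, or convincing evidence, that dual is better than single.

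The cost is revised text and a settled post-hoc method. The downside is that the stated power for two contrasts becomes visibly less favourable.

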### Interventions and comparison

#### Rationale for acupuncture protocol

On the day before surgery, patients are randomly assigned to the dual-acupoint TEAS group (DT), the single-acupoint TEAS group (ST) or the Control group, stratified by study center with a central computer-generated scheme. For all the patients, the electrodes (5 × 5 mm^2^) are placed at bilateral ST36 (*Zusanli*) and BL13 (*Feishu*), and then connected to the Hwato Electric Acupuncture Treatment Instrument (model No. SDZ-V; Suzhou Medical Appliances Co, Ltd., Suzhou, China). Thirty minutes before surgery, the intervention is performed by an investigator who is not involved in anesthesia and follow-up. For group DT, ST36 and BL13 are stimulated. For group ST, only ST36 is stimulated. For the Control group, electrodes are attached but no stimulation is given.

ST36 and BL13 are chosen and identified according to ancient Chinese medical books. ST36 is the most often used acupoint for abdominal surgery, and BL13 may benefit the respiratory system. ST36 is located on the anterior aspect of the leg, at 3 *cun* (Chinese inch) below the kneecap and 1 *cun* from the anterior crest of the tibia. BL13 is located at 1.5 *cun* lateral to the spinous process of the third thoracic vertebrae. One *cun* is defined as the width of the patient’s thumb (see supplementary material 2). The patients in the DT and ST groups receive electrical stimulation with the “disperse-dense” waves of alternating frequencies of 2 and 15 Hz for a 2-s cycle. Increasing electrical stimulation intensity (7–11 mA) will be applied to identify the threshold intensity, defined as perception of the “*Teh Chi*” sensations of heaviness, numbness, and swelling in their crura. Electric stimulation is administered 30 min prior to surgery and continued until the end of the surgery. Patients in the Control group receive the same treatment without electric stimulation.

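### The ITT set is really a modified ITT conditioned on treatment, and the per-protocol rules make no exception for death although mortality is analysed in that set

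*Protocol article*

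**What the plan says.** All references are to the protocol article.

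- **Sample size calculation and statistical analysis.** The ITT population is "defined as the patients who are randomized and received at least one treatment session". The PP population is "defined as the patients who completed the study and did not have major protocol violations". The two are used throughout: "All analyses were based on the ITT population and the PP population". Their relation is then given: "The result of the ITT analysis will be compared with that of the PP analysis to check whether the results are consistent".
- **Operative details.** Patients are left out of what is called the protocol analysis if they were ineligible, or if they "had no in-hospital evaluation of the outcomes or had no follow-up visit". The natural reading is that this means the PP analysis. Death is not mentioned.
- **Rationale for acupuncture protocol.** "On the day before surgery, patients are randomly assigned". The single session follows at the operation: "Electric stimulation is administered 30 min prior to surgery and continued until the end of the surgery". In the dual-acupoint (DT) and single-acupoint (ST) arms the current is raised until the patient perceives a defined sensation. Control patients go through the same procedure without current.
- **Outcome measurement.** Secondary outcomes include "all-cause mortality within 30 days and 1 year after surgery".
- **Design.** Follow-up lasts 1 year, with assessments at baseline, days 1, 3 and 30, and 1 year.

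**The concern.** Two separate things go wrong when the definitions are followed as written.

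First, receiving the session is an event after randomisation. A patient who has surgery without the session has a 30-day outcome and an assigned arm, but is not counted. The reasons can differ by arm: only DT and ST patients have current raised while awake, so only they can decline because of what they feel. The article also does not say whether an abandoned session counts as received. The set carries the ITT name without the ITT property.

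Second, a patient who dies may have no follow-up visit and may not have completed a one-year study. Excluding such patients from a set in which mortality is analysed removes the outcome from its own numerator. It can also remove patients whose pulmonary complication preceded death. A check that compares a set conditioned on treatment with a set conditioned on survival or attendance says little about robustness, whether or not the two agree.

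**Working it through.** **1. The plan's own figures.** Planning rates are 32% (Control), 23% (ST) and 14% (DT), with 115 per arm and 345 in total. The usual two-proportion formula for 32% v 14%, two-sided with 80% power, is

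n = [z(α/2)·√(2p̄q̄) + z(β)·√(p₁q₁ + p₂q₂)]² / (p₁ − p₂)².

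It gives 85 per arm at α = 0.05 and 114 at α = 0.05/3. So 345 is nearly reproduced (3 × 114 = 342), though only with an adjustment that the text does not state. This point does not contest the sample size. The counts used below are 115 × 0.32 = 36.8, about 37, and 115 × 0.14 = 16.1, about 16.

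**2. Who leaves the ITT set.** There are two routes to being randomised but untreated:

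- The operation is cancelled. There is then no postoperative outcome, and leaving the patient out is defensible.
- The operation goes ahead without the session. The patient has an outcome and should be counted.

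The article gives no rate for either. If 3–5% were untreated by both routes together, 345 × 0.03 to 0.05 = 10 to 17 patients would be outside the set, and only an unknown part of them would be recoverable.

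To size the effect, suppose 3–5% of DT patients had surgery untreated and had the Control rate. The DT rate over all operated patients would be 0.97 × 14 + 0.03 × 32 = 14.5%, or 0.95 × 14 + 0.05 × 32 = 14.9%, instead of 14%. That is a shift of under 1 point, unless the untreated also differ in prognosis.

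**3. Which deaths leave the PP set.** This depends on undefined words.

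| Reading | Deaths removed from PP |
|---|---|
| Completing the study means attending the 1-year visit | All deaths up to 1 year; PP mortality is zero in every arm |
| A follow-up visit means day 30 or later | Deaths before the day-30 visit; later deaths stay |
| Days 1 and 3 count as follow-up visits | Only deaths before any such assessment |

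The third reading is weakened because Operative details lists in-hospital evaluation separately from the follow-up visit. The second and third rows concern that section's rule alone; the completion condition applies as well.

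**4. Effect on the primary outcome in PP.** The article gives no mortality. Assume 1–5% at 30 days: 115 × 0.01 to 0.05 = 1 to 6 deaths per arm. Assume also that each removed patient had a pulmonary complication.

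| Removed | Control | DT | Difference (points) | Risk ratio |
|---|---|---|---|---|
| None | 37/115 = 32.2% | 16/115 = 13.9% | 18.3 | 0.43 |
| 3 per arm | 34/112 = 30.4% | 13/112 = 11.6% | 18.8 | 0.38 |
| 6, Control only | 31/109 = 28.4% | 16/115 = 13.9% | 14.5 | 0.49 |
| 6, DT only | 37/115 = 32.2% | 10/109 = 9.2% | 23.0 | 0.29 |

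Equal losses barely move the risk difference, although they flatter the risk ratio. Unequal losses move both, in either direction.

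**The case against.** The case against is substantial, and much of it stands.

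- A reader might infer that a treatment session has no meaning in the Control arm. The text does not support this: Controls have electrodes attached and go through the same procedure without current, so the condition can be applied in every arm.
- A reader might infer that an unblinded operator decides who is excluded. The person delivering the session must know the arm, but nothing says that this person decides whether surgery proceeds or who is analysed. The surgeons and anaesthetists are to be kept blinded by an opaque box.
- A reader might infer that PP mortality is near zero by construction. That needs completion to mean the 1-year visit, which the article does not say. The rule in Operative details removes only patients with no follow-up visit at all. Death is not named in either rule, so its removal is a literal reading and not a stated intention.
- A reader might infer that either set could be presented as the main result. ITT is defined first and PP is described as a consistency check, and a full analysis plan commonly names the primary set.
- Most untreated patients may be cancelled operations, which any sensible rule would also leave out.

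What remains is that the definitions the article does give are wrong as written. One attaches the ITT name to a treated subset. The other sends mortality through a set that has no rule for the dead. These are stated rules, not details left to another document.

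**Conclusion.** The point holds in a limited form. The ITT population is a modified ITT that can drop operated patients whose stimulation was not delivered, possibly at different rates by arm. The PP rules, read literally, remove some deaths, and on one reading all deaths up to 1 year. PP mortality and the ITT-versus-PP check therefore cannot be interpreted as planned.

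It would go too far to say that the main comparison has lost the protection of randomisation. Treated patients who die stay in the ITT set, the number operated but untreated is unknown and may be small, and equal losses of three per arm shift the risk difference by about 0.5 points. The effect on the primary outcome is probably small unless losses differ by arm; six losses confined to one arm would shift it by 4 to 5 points. All these sizes rest on assumed rates of non-treatment and death, and on the assumption that every removed patient had a complication.

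**What to change.** - Define the primary set as all randomised patients who have surgery, analysed in the assigned arm whether or not stimulation was delivered. The only exclusion is an operation cancelled before electrodes are attached, with the number counted and reported by arm.
- Name this set as primary for every outcome. If the treated subset is kept, call it modified ITT.
- Restrict PP to a sensitivity analysis of the 30-day pulmonary outcome, and do not analyse mortality in it.
- In both Operative details and the statistical section, state that death is an observed outcome and counts as completed follow-up, so that it is never a reason for exclusion.

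The cost is wording and a tabulation of exclusions by arm. Including a few untreated patients may slightly dilute the estimated effect. When the article was submitted, 113 patients had been recruited and the interim analysis was set at 173, so the change could then have been made before any comparative look.

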### Design

We adhered to the Standard Protocol Items: Recommendations for Interventional Trials (SPIRIT) guidelines in the preparation of this protocol (see Fig. 1 and Additional file 1 for the SPIRIT Figure and Checklist, respectively). The trial is an investigator-initiated, multicenter, randomized clinical trial comparing treatment with dual-acupoint TEAS versus single-acupoint stimulation and no-stimulation before and during anesthesia in elderly patients undergoing gastrointestinal surgery. Three hundred and forty-five participants will be included from the following four hospitals: First Affiliated Hospital of Fourth Military Medical University (Xijing Hospital); Second Affiliated Hospital of Guangzhou University of TCM; First Affiliated Hospital of Chongqing Medical University; and First Affiliated Hospital of Zhengzhou University. These participants will be randomly assigned to three groups through central randomization in a 1:1:1 ratio. The central randomization system will be used and performed by the Department of Anesthesiology of Xijing Hospital. In each center, an investigator who is not involved in anesthesia and follow-up will perform the randomization. This investigator logs into the central randomization system and inputs the patient’s information, then a random number and group assignment will be immediately given by the system. According to the assignment, the patients will receive interventions from 30 min before anesthesia induction to the end of the surgery. The follow-up period lasts for 1 year. Outcomes are assessed at baseline and 1, 3, and 30 days, and 1 year after surgery.

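### Randomization is stratified by center but the primary chi-square test is unadjusted; if center rates differ, this is mildly conservative and gives up a little power

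*Protocol article*

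**What the plan says.** The Design section of the Protocol article states: "Three hundred and forty-five participants will be included from the following four hospitals". It continues: "These participants will be randomly assigned to three groups through central randomization in a 1:1:1 ratio". The section on the rationale for the acupuncture protocol adds that assignment is "stratified by study center with a central computer-generated scheme". Neither section mentions blocks or any other device for balance within a center.

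Under Outcome measurement, the primary outcome "is postoperative pulmonary complications occurring within 30 days after surgery". The section on sample size and statistical analysis then fixes the test: "We compare both the composite primary outcome of incidence of postoperative pulmonary complications within 30 days after surgery", together with a secondary outcome on systemic inflammatory response syndrome, "by postoperative day 30 with an unadjusted" chi-square test. Comparisons between groups follow by a post-hoc method that is not named. The article mentions no center-stratified or center-adjusted analysis of the primary outcome, not even as a sensitivity analysis.

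**The concern.** When arms are balanced within centers, differences between centers drop out of the treatment contrast. A pooled chi-square nevertheless computes its variance from the overall event rate, so that variance still contains the between-center part. The standard error is then larger than it needs to be, the P value tends to be too high, and some power is lost.

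The loss would fall on a trial with little to spare in one of its two questions. Whether dual-acupoint stimulation beats single-acupoint stimulation is half of the stated hypothesis, and that comparison has low power at 115 per arm. The analysis section chooses the unadjusted test in so many words, so this is a stated choice that does not follow the design, not a detail left to a separate analysis plan.

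**Working it through.** **Inputs from the article.** Four hospitals, 1:1:1 allocation, 115 per arm (345 in all), 80% power, two-sided 0.05. The planning rates, in the section on sample size, are 32% for Control and 23% for single acupoint (both from a pilot), and 14% assumed for dual acupoint. The average of 14%, 23% and 32% is 23%.

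**Inputs assumed.** Event rates by center (the article gives none), near-equal center sizes (29, 29, 29 and 28 per arm), exact balance within center, and a common treatment shift on the logit scale. The pairwise figures also assume a chi-square at an unsplit 0.05, because the post-hoc method is not named.

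**The plan's own sample size.** The pooled-variance formula is n = [z(α/2)·√(2p̄q̄) + z(β)·√(p₁q₁ + p₂q₂)]² / (p₁ − p₂)². For Control 32% against dual 14% at α = 0.05/3: [2.394 × 0.595 + 0.842 × 0.581]² / 0.18² ≈ 113.1, so 114 per arm, close to 115. The article does not state this split of α. At an unsplit 0.05 the same comparison needs 85 per arm and the three-arm 2-df test needs 106. The present point does not depend on which route was used.

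**Power for dual versus single as planned.** With 23% against 14% and 115 per arm: (0.09 × √115 − 1.96 × 0.549) / 0.545 = −0.204, which gives a power of 41.9%.

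**Why the pooled test is conservative under balance.** The pooled variance per patient is p(1 − p) = 0.23 × 0.77 = 0.1771. With balance within center, only the within-center part applies, 0.1771 − s², where s² is the variance of the center rates. The ratio is r = 1 − s²/0.1771. The true size of the nominal 5% test is approximately 2 × [1 − Φ(1.96/√r)]. For rates of 13, 20, 26 and 33%: s² = (0.10² + 0.03² + 0.03² + 0.10²)/4 = 0.00545, r = 0.969, 1.96/√r = 1.991, size about 0.047.

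**Pairwise results.** Simulation of 200,000 trials with exact balance, unadjusted against center-stratified Cochran-Mantel-Haenszel (CMH):

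| Assumed center rates | r | Size, formula | Size, simulated (unadjusted v CMH) | Dual v single power (unadjusted v CMH) |
|---|---|---|---|---|
| about 18, 21, 25, 29% | 0.991 | 0.049 | 0.051 v 0.051 | 42.3% v 42.5% |
| 13, 20, 26, 33% | 0.969 | 0.047 | 0.047 v about 0.05 | 42.4% v 43.2% |
| 8, 18, 28, 38% | 0.929 | 0.042 | 0.043 v about 0.05 | 42.2% v 44.3% |
| 5, 15, 30, 42% | 0.887 | 0.038 | 0.038 v about 0.05 | 41.8% v 45.4% |

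The differences in power are 0.2, 0.8, 2.1 and 3.6 points.

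**Overall three-arm test (2 df), exact balance, 100,000 trials.** Unadjusted v CMH:

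| Assumed center rates | Size | Power at 14/23/32% |
|---|---|---|
| equal | 0.050 v 0.050 | 84.6% v 84.5% |
| 18–29% | 0.048 v 0.048 | 84.8% v 84.9% |
| 12–37% | 0.043 v 0.050 | 85.2% v 86.5% |
| 7–45% | 0.035 v 0.051 | 85.7% v 88.8% |

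Blocks of 6 in place of exact balance give a size of 0.044 at 12–37% and 0.034 at 7–45%, the same picture.

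**Without balance within center.** With simple randomization inside each center, the unadjusted 2-df test has a size of 0.050, 0.049 and 0.049 at the mild, moderate and strong spreads. Its power is 84.5% v 84.4%, 84.5% v 86.3% and 84.4% v 88.2% for CMH. The conservatism disappears, and CMH gains power only at the wider spreads.

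**The case against.** The strongest reply is that the loss is hypothetical and small, and that it errs on the safe side. Nothing in the article shows that center rates differ. At a spread of 18–29% the two tests are indistinguishable, and the widest case, 5–42%, is an eightfold spread with no support in the text. The article also describes no blocking, and without balance within center the size stays near 0.05. Even at the wider spreads the dual versus single comparison moves only from about 42% to 43–45%, and it remains badly underpowered. All of this stands, and it is why the point is minor.

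It does not remove the point. Stratifying normally implies some restriction within strata, and blocks of 6 reproduce the conservatism. Differences between four separate hospitals are plausible, and the assumed rates come from a pilot in one of them. Center is known for every patient, and with balanced allocation and equal center rates the stratified test costs nothing measurable (84.6% v 84.5%).

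A reader might infer that the 5% level and the 95% confidence intervals of this trial are wrong, or that the unadjusted test is invalid after stratified randomization. The article supports neither. Both would need center differences that it does not report and balance that it does not describe, and even then the error is only toward caution.

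**Conclusion.** The mismatch between design and analysis is real and is stated in the article. Its consequence is conditional on two things: event rates must differ between centers, and allocation must be balanced within them. If both hold, the unadjusted test has a true size of about 0.047 to 0.038 and loses from under 1 to about 4 points of dual versus single power over assumed spreads from 13–33% to 5–42%. If centers differ only mildly, nothing material is lost. If allocation is not balanced within center, the size stays near 0.05 and only the power gain at wider spreads remains.

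False positives are not inflated. Adopting the stratified test should not be presented as a remedy for the low power of the dual versus single comparison. Severity: minor.

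**What to change.** In the analysis section, replace the unadjusted chi-square as primary analysis with the Cochran-Mantel-Haenszel test stratified by the four centers: the 2-df general association test overall and the 1-df test for each pair. Report Mantel-Haenszel risk differences with 95% confidence intervals, and keep the unadjusted chi-square as a sensitivity analysis. State in the same place whether allocation is blocked within center.

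Because the published article itself fixes the test, the change needs a dated amendment, with any separate analysis plan brought into line. It should be in place before any unblinded data are seen, including the interim analysis at n = 173; 113 participants had been recruited when the article was written. The cost is the amendment and the wording. No extra patients, visits or data are needed, since center is already recorded as the stratification factor.
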